#### Control group

Participants allocated to the control group (CTRL-Group) carry out a 40’/day home-based self-treatment program consisting of muscle-stretching and active mobilization exercises for 40’/day for 6 consecutive weeks, from Monday to Friday. Participants receive detailed exercises instructions and a diary where exercises performed, any side effects and/or specific difficulties ran into the program should be noted. One training session will be given to the participants allocated in the control group in order to learn how to perform home exercises.

### Outcomes and measurement

The primary outcome of this study is changes in molecular biomarkers levels (blood biomarkers and serum NDEVs derived biomarkers) in response to an intensive multidisciplinary rehabilitation treatment in PwPD (see Table 1). Secondary outcomes include changes in motor and non-motor symptoms, balance and gait performance, aerobic capacity, and cognitive functioning (see Table 2).

**Table 1 pone.0309405.t001:** Primary outcomes and instruments to assess the study variable.

Primary Outcome measures	Instruments to assess the study variable
**Blood Biomarkers**	**Serum biomarkers in NDEVs** Oligomeric α-synuclein (α-syn) ng/ml; SNARE complex: Syntaxyn-1(STX-1A) (ng/ml), VAMP-2 (ng/ml) and SNAP-25 (ng/ml); Brain-Derived Neurotrophic Factor (BDNF) (ng/ml); Pro-BDNF (ng/ml); Glial cell line-derived Neurotrophic factor (GDNF) (ng/ml); Cerebral dopamine neurotrophic factor (CDNF) (ng/ml). **Pro-inflammatory** [IL-1β (pg/ml), Tumour Necrosis Factor alpha (TNFα) (pg/ml), Interferon gamma (IFN-γ) (pg/ml), IL-6 (pg/ml), IL-18 (pg/ml)], Anti-inflammatory (IL-10) (pg/ml) cytokines.

**Table 2 pone.0309405.t002:** Secondary outcomes and instruments to assess the study variable.

Secondary Outcome measures	Instruments to assess the study variable
**Functional assessment and motor function**	• The Movement Disorders Society Unified Parkinson’s Disease Rating Scale (MDS-UPDRS) Part I-IV • Timed-Up and Go test (TUG) • 6-Minute Walk Test (6-MWT) • 10-Meter Walk Test (10MWT) • 5-Time Sit-To-Stand (5TSTS) • Modified Dynamic Gait Index (mDGI) • Gait analysis (using a 9-camera SMART-D motion capture system (Optional)
**Cognitive functioning**	• Montreal Cognitive Assessment (MoCA Test) • Mini-Mental Parkinson (MMP) • Forward Verbal Span • Backward Verbal Span • Immediate and delayed story recall test • Rey’s Figure–Recall • Rey-Osterrieth Complex Figure Copying Test • Frontal Assessment Battery (FAB) • Raven Coloured Progressive Matrices (CPM-47) • Attentive Matrices • Alternate Verbal Fluency • Verbal fluency test (phonemic and semantic tasks) • Trail Making Test (TMT) • Symbol Digit Modalities Test (SDMT) (Oral Version) • Stroop Test-Short Version • Boston Naming Test • Gesture Imitation Test (IMA-T)
**Non-motor symptoms**	• Non-Motor Symptoms Scale (NMSS) • Parkinson Fatigue Scale (PFS) • Epworth Sleepiness Scale (ESS) • Pittsburgh Sleep Quality Index (PSQI) • REM sleep behavior disorder screening questionnaire (RBDSQ) • Italian version of the Composite Autonomic Symptoms Score (COMPASS-31) • Numeric Rating Scale (NRS) • The Parkinson Disease Questionnaire (PDQ-39) • Beck Depression Inventory-II (BDI-II) • State-Trait Anxiety Inventory. Forma Y (STAI-Y) • Dimensional Apathy Scale (I-DAS) • Snaith-Hamilton Pleasure Scale (SHAPS) • Barratt Impulsiveness Scale-11 (BIS-11) • Toronto Alexithymia Scale (TAS-20) • Questionnaire for Impulsive-Compulsive Disorders in Parkinson’s disease (QUIP-RS-IT) • NeuroPsychiatric Inventory Questionnaire (NPI-Q)
**Daily self-care activities**	• Activities of Daily Living (ADL) • Instrumental Activities of Daily Living (IADL)

Each participant undergoes assessments before (T1), at the end of treatment (T2) and 3 months after the end of treatment (T3). The measures use for these assessments, applied at each timepoint, are detailed in Fig 1.

At the baseline a researcher collects socio-demographic data from each participant (i.e., age, gender, education level and hand dominance). Then, blood sample collection and assessment of disease severity, cognition, motor and non-motor symptoms are performed at T1, T2 and, T3.

### Data management

Signature of informed consent, data collection, and the experimental treatment are conducted in person.

Each patient is given an identification code to guarantee their anonymity in the study. Separate storage is made for a list of identification codes. Descriptive data are gathered and stored in data files on protected computer networks.

Blood samples are delivered at the Laboratory of Molecular Medicine and Biotechnology (LAMMB) of the IRCCS Fondazione Don Carlo Gnocchi ONLUS—S. Maria Nascente in Milan where they are marked with an anonymous code, and then processed for serum storage and NDEVs enrichment (See S1 and S2 Appendices). All anamnestic, clinical, and biological data are collected in an anonymized database with a progressive number code and analyzed as aggregate data. Signed informed consent and all clinical documents are stored in a guarded archive in the PI office.

### Monitoring

The research team has expertise in a variety of disciplines, such as medical and behavioral management, patient engagement, biostatistics, quantitative and qualitative outcomes assessment and analysis.

The local ethics committee does not require a data monitoring committee due to the short duration and minimal risks involved in this rehabilitation program.

The team records any adverse events that participants report, assesses them internally to prevent future ones, and reports them as part of the planned publication.

Since there are no sponsors for the study, it is not necessary to provide information on the frequency and procedures for reviewing the study process. Weekly meetings are held by the project management group to discuss the current status of data collection and address potential problems and difficulties.

### Data analysis

The analyses will be conducted using SAS software version 9.4 and R software version 4.2.1. We will conduct a descriptive analysis of the two treatment groups, including the mean and standard deviation for normally distributed variables and the median and interquartile range for variables deviating significantly from normality. To assess the treatment effect, we will employ an analysis of covariance (ANCOVA) model [44], incorporating covariates (gender, age, and disease duration) to adjust the estimates. This model will be utilized to evaluate the treatment effect both at the conclusion of the treatment period and at the end of follow-up time. The parametric approach will be applied for primary outcomes, characterized by continuous scales. Concerning secondary outcomes, non-parametric tests (Wilcoxon rank-sum test) will be employed for those assessed with ordinal scales. Estimates of primary outcomes will be adjusted using False Discovery Rate correction [45]. A 95% confidence interval will be employed, and statistical significance will be reported for any observed differences between groups with a significance level set at p < 0.05. Subgroup analyses will be conducted to examine whether the treatment exhibits a differential effect based on the severity of the patient, as determined by baseline values of the Hoehn and Yahr scale or UPDRS III scale.

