### Sample size

There are currently no clinical studies examining the effectiveness of rehabilitation treatment on our primary outcomes. Therefore, the sample size was determined based on the preliminary results of a recent cross-sectional study by Agliardi and colleagues [36]. In Agliardi’s study a total of 32 PD patients were consecutively recruited and screened and a total of 40 healthy subjects were included as controls using frequency matching for age and gender. The main objective of this study was to identify differences in NDEs derived oligomeric α-Synuclein concentration between PD and healthy controls subjects. Hence, considering 2 degrees of freedom with 80% power; 0,05 alpha and a drop-out percentage of 20%, we planned a sample size of N = 72 (N for each group = 36) that will be more than adequate to control for a potential participants’ drop out.

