### Randomization and blinding

Once recruited, participants are randomly allocated to two different groups, the Experimental (EXP-Group = 36) and the Control Group (CTRL-Group = 36). A sample block randomization method is employed. The random allocation table is generated by computer and stratified based on PD stages according to mH&Y classification (from 1.5 to 3).

The study involves a single-blind procedure; the allocation of subjects to intervention or control groups is blinded to assessors. Participants are blinded to the benefits of each intervention and the study hypothesis.

Blinded assessments are performed at T1, T2, and T3 by a movement disorder specialist.

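### The stated ANCOVA leaves out the outcome's own T1 value (and, less importantly, the mH&Y stratification factor), which costs precision but does not bias the treatment effect

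*Protocol article*

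**What the plan says.** The Data analysis section names the model and its covariates: an ANCOVA "incorporating covariates (gender, age, and disease duration) to adjust the estimates". On timing it adds: "This model will be utilized to evaluate the treatment effect both at the conclusion of the treatment period and at the end of follow-up time". Its dependent variable is not stated. Under Outcomes and measurement, "The primary outcome of this study is changes in molecular biomarkers levels", which points towards change scores but does not settle what the ANCOVA models.

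Two design features bear on that list. Every biomarker has its own baseline, because "blood sample collection and assessment of disease severity, cognition, motor and non-motor symptoms are performed at T1, T2 and, T3" (Outcomes and measurement). The allocation table is "stratified based on PD stages according to mH&Y classification (from 1.5 to 3" (Randomization and blinding).

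Neither the T1 value nor the stage is among the covariates. Baseline severity enters the analysis only to define subgroups, "as determined by baseline values of the Hoehn and Yahr scale or UPDRS III scale".

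**The concern.** A biomarker's own earlier value is usually a much better predictor of its later value than gender, age or disease duration. A model without it leaves explainable variation in the error term. With roughly 29 evaluable participants per arm, that loss matters for every primary comparison, and Table 1 of the article lists 14 biomarkers.

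A chance T1 difference between the arms is also handled imperfectly. A level analysis leaves part of it in the estimate, and a change analysis subtracts too much.

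The stratification factor is a lesser matter. Stratifying makes the arms more alike on stage, and a model that ignores stage does not credit that gain, so its standard errors are too large if stage predicts the biomarker.

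The covariate list is written out as a specific set, with no wording that marks it as a selection. It is therefore a stated choice and not a detail left open.

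**Working it through.** **Inputs.** From the article: 36 per arm, 1:1 allocation, alpha 0.05, power 80%, 20% dropout. Assumed, because the article does not give them: a two-sided test, equal outcome variance at T1 and T2 (set to 1), and a within-arm T1–T2 correlation r of 0.3 to 0.7. If gender, age and disease duration explain part of the outcome, r is the correlation that remains after them.

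**The plan's own figure.** N = 72 cannot be reproduced, because the Sample size section gives no effect size or SD. Working backwards, 36 × 0.8 = 28.8, about 29 evaluable per arm. The effect detectable with 80% power is (1.960 + 0.842) × √(2/29) = 0.74 SD by the normal approximation, for an analysis of the T2 level without T1. This effect is inferred and is not stated in the article.

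**Variance under each model.** Level without T1: 1. Change without T1: 1 + 1 − 2r = 2(1−r). T2 level adjusted for T1: 1−r². The penalty relative to the adjusted model is 1/(1−r²) for level and 2(1−r)/(1−r²) = 2/(1+r) for change.

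| r | Level | Change | T1-adjusted | Penalty, level | Penalty, change |
|---|---|---|---|---|---|
| 0.3 | 1 | 1.40 | 0.91 | 1.10 | 1.54 |
| 0.5 | 1 | 1.00 | 0.75 | 1.33 | 1.33 |
| 0.7 | 1 | 0.60 | 0.51 | 1.96 | 1.18 |

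**Power, 29 per arm.** The effective effect is d/√(variance). The first three columns use the inferred d = 0.74 (normal approximation); the last three use an assumed d = 0.5 (noncentral t).

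| r | Level, 0.74 | Change, 0.74 | Adjusted, 0.74 | Level, 0.5 | Change, 0.5 | Adjusted, 0.5 |
|---|---|---|---|---|---|---|
| 0.3 | 80.0% | 65.8% | 83.6% | 46.5% | 35% | 50% |
| 0.5 | 80.0% | 80.0% | 89.9% | 46.5% | 47% | 58% |
| 0.7 | 80.0% | 95.1% | 97.5% | 46.5% | 68% | 75% |

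**Chance imbalance at T1.** Its standard error is √(2/29) = 0.26 SD, and the probability that it exceeds 0.25 SD in either direction is 34%. Given an imbalance of 0.25 SD, the expected shift in the estimate is:
- level: +0.25r, that is +0.075, +0.125, +0.175 SD at r = 0.3, 0.5, 0.7;
- change: −0.25(1−r), that is −0.175, −0.125, −0.075 SD, through regression to the mean;
- T1-adjusted: none, if the relation is linear.

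**Omitting mH&Y.** This was checked by simulation: 4,000 runs per scenario, 29 per arm, four stage strata balanced between arms, three uninformative covariates, and an assumed stage–outcome correlation of 0.3 to 0.5. Stage was entered as a linear score. Adding it to the T1-adjusted model changed power by about 0 to +2.5 percentage points. A level analysis with neither T1 nor stage had a type I error of about 2.7% to 4.2%; with both it was about 5%.

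**The case against.** The strongest reply is that the article does not exclude baseline adjustment. In a before-and-after design, ANCOVA often means a comparison adjusted for baseline, and the parenthesis might list only additional covariates. The article also condenses a fuller protocol that is not shown. This lowers confidence about what the trial team intends. It does not remove the point, because an analyst who follows the published sentence would fit three covariates and would have to guess the dependent variable.

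Second, the primary outcome is defined as change, so T1 is probably used by subtraction and the level figures may not apply. That is fair. On the change reading the loss shrinks as r rises: at d = 0.74 and r = 0.7 it is 95.1% against 97.5%. On the level reading it is small at low r: 46.5% against 50% at d = 0.5 and r = 0.3. Neither reading avoids a loss for r strictly between 0 and 1, apart from the degree of freedom that adjustment uses.

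Third, a reader might infer more than the text supports:
- *That the estimate is biased.* Level, change and T1-adjusted estimators are all unbiased over repeated randomisation, and ordinary standard errors already allow for chance imbalance.
- *That a T1 imbalance carries over in full.* Only a fraction r does (level), or 1−r with the opposite sign (change).
- *That omitting the stratification factor invalidates the tests.* It makes them conservative, and only if stage is prognostic, which the article does not establish. Stratification already limits imbalance on stage.

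**Conclusion.** The point holds as a loss of efficiency in a model that is stated and under-specified. The T1 omission carries most of the weight. It inflates the variance by 1.10 to 1.96 (level) or 1.54 to 1.18 (change) as r goes from 0.3 to 0.7. At the effect that N = 72 can detect on a level analysis, that is 3.6 to 17.5 percentage points of power on the level reading (83.6 − 80.0 and 97.5 − 80.0) and 17.8 to 2.4 points on the change reading (83.6 − 65.8 and 97.5 − 95.1). The mH&Y omission is secondary, at about 0 to 2.5 points.

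The direction of the loss needs only 0 < r < 1 and equal variances at T1 and T2. Its size rests on the assumed r, on 29 evaluable per arm, and for mH&Y on an assumed association between stage and biomarker. The T3 comparison follows the same formulas with its own T1–T3 correlation.

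**What to change.** Before database lock, replace the model sentence with a full specification:
- dependent variable: the T2 value of the outcome and, in a separate model, the T3 value;
- terms: treatment, the T1 value of the same outcome, the mH&Y stratum as used in randomisation (categorical), age, gender and disease duration;
- the same model for the continuous secondary outcomes.

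If baseline adjustment was always intended, this only puts it in writing.

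N = 72 does not change and no extra sampling is needed, since T1 blood draws are already scheduled; at publication recruitment was still under way. With 58 evaluable participants the listed model leaves 58 − 5 = 53 residual degrees of freedom (intercept, treatment and three covariates). The T1 value uses one more and, if stages 1.5, 2, 2.5 and 3 each form a stratum, stage uses three, leaving 49. The wording should be settled before results are seen, because covariates added afterwards would look data-driven.

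### Ordinal-scale secondary outcomes are assigned to a plain Wilcoxon rank-sum test, which is valid but less precise than an analysis adjusted for the T1 score and mH&Y stratum

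*Protocol article*

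**What the plan says.** The Data analysis section assesses the treatment effect at the end of treatment and at the end of follow-up by an "analysis of covariance (ANCOVA) model [44], incorporating covariates (gender, age, and disease duration) to adjust the estimates". It then divides the outcomes: "The parametric approach will be applied for primary outcomes, characterized by continuous scales", whereas for secondary outcomes "non-parametric tests (Wilcoxon rank-sum test) will be employed for those assessed with ordinal scales". It names no stratified version of the rank test, no ordinal or rank model with covariates, and no effect estimator for these outcomes. A general sentence says that 95% confidence intervals will be used.

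Three other places bear on this:

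- Under Randomization and blinding, allocation is stratified by mH&Y stage, from 1.5 to 3.
- Under Outcomes and measurement, "Secondary outcomes include changes in motor and non-motor symptoms, balance and gait performance, aerobic capacity, and cognitive functioning". The Abstract also describes the secondary outcomes as changes.
- The same section says that "blood sample collection and assessment of disease severity, cognition, motor and non-motor symptoms are performed at T1, T2 and, T3", so a baseline value of each scale is planned for every participant.

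The Data analysis section does not say whether the rank-sum test is applied to T2 and T3 scores or to changes from T1.

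**The concern.** The rank-sum test compares two groups on one variable and has no place for covariates or strata. For outcomes on ordinal scales, the article therefore fixes an analysis that omits the stratification factor and the three covariates it considers worth adjusting for elsewhere. The T1 score of the same scale would be expected to be a strong predictor of the later score. Here it is unused if T2 scores are ranked, and enters only as a fixed subtraction if changes are ranked.

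This matters because many of the symptom scales in Table 2 (the MDS-UPDRS parts, NMSS, PDQ-39 and BDI-II, for example) are built from ordinal items and would plausibly fall under the rule. Motor and non-motor symptoms are part of the stated objective. With 36 per arm before dropout, avoidable loss of precision can decide whether a moderate clinical effect is seen.

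**Working it through.** **Inputs from the protocol article.** 36 per arm, 20% dropout, alpha 0.05, power 80% (Sample size section). Evaluable per arm: 36 × 0.8 = 28.8, taken as 29. Two-sided testing is assumed, as the article does not state sidedness.

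**The article's own figure.** N = 72 was set for the primary biomarkers, with no effect size or SD stated, so it cannot be reproduced, only solved backwards. For a comparison of two means, d = (1.960 + 0.842) × √(2/n): 0.74 SD at n = 29 and 0.66 SD at n = 36. No figure is given for the ordinal outcomes.

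**Assumptions.** Effect 0.5 SD; T1–T2 correlation r of 0.3 to 0.8. The article gives neither.

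**Why the analyses differ.** Take the variance of the T2 score as 1. The variance relevant to the group comparison is then:

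- T2 score: 1
- change from T1: 2(1 − r)
- adjusted for T1: 1 − r²

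The ratio of adjusted to T2 score is 1 − r². The ratio of adjusted to change is (1 − r²) / [2(1 − r)] = (1 + r)/2. These ratios are also the approximate relative sample sizes, and they do not depend on n.

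| r | adjusted / T2 score | adjusted / change |
|---|---|---|
| 0.3 | 0.91 | 0.65 |
| 0.5 | 0.75 | 0.75 |
| 0.7 | 0.51 | 0.85 |
| 0.8 | 0.36 | 0.90 |

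Both ratios are below 1 for any r between 0 and 1, so adjustment gains on either reading of the article.

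**Simulated power.** 29 per arm, effect 0.5 SD, 4,000 trials per setting. Simulation A used a 20-level ordinal score. Simulation B is a second run at r = 0.5 to 0.8. Each cell shows A, then B.

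| r | Wilcoxon on T2 | Wilcoxon on change | Rank ANCOVA on T1 |
|---|---|---|---|
| 0.3 | 44.4% / – | 31.3% / – | 47.5% / – |
| 0.5 | 44.1% / 44% | 39.7% / 44% | 53.1% / 54% |
| 0.7 | 44.0% / 43% | 58.9% / 63% | 68.1% / 68% |
| 0.8 | 44.9% / 44% | 76.1% / 82% | 81.7% / 82% |

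The simulation standard error near 50% is √(0.5 × 0.5 / 4000) = 0.8 points. The 4 to 6 point gaps between A and B for change scores exceed that, so both values are kept as a range.

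**Loss against rank ANCOVA, in power points** (r = 0.5 / 0.7 / 0.8):

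- If T2 scores are ranked: 9–10 / 24–25 / 37–38.
- If changes are ranked: 10–13 / 5–9 / 0–6.

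**Validity.** With no true effect, simulation A rejected in 4.2% to 5.2% of trials across all three methods.

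**A larger effect.** Taking Wilcoxon efficiency as 3/π, Wilcoxon on T2 reaches 80% power at d = 2.802 × √(2 / (29 × 0.955)) = 0.753. At that effect and r = 0.5 / 0.7 / 0.8, the normal approximation gives 80% / 95% / 99% for Wilcoxon on change and 91% / 98% / 99.8% for adjusted analysis. The adjusted figures carry no 3/π factor, so they slightly favour adjustment.

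**Limit.** Only T1 is modelled. Any gain from mH&Y stage, gender, age or disease duration is not quantified.

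**The case against.** The strongest defence is that a rank test is a conventional choice for ordinal scales, that it holds its level under randomization, and that these are secondary outcomes with no power claim. All of that stands. So does the fact that 29 per arm is a scenario: the Discussion expects few dropouts. The variance ratios above do not depend on that number, however.

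A reader might infer several stronger statements that the article does not support:

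- *The T1 score is ignored.* This is not established. Outcomes and measurement and the Abstract define the secondary outcomes as changes, and ranking changes does use T1. The largest losses above apply only if T2 scores are ranked.
- *The test yields only a p-value.* A Hodges-Lehmann shift with a confidence interval goes with it, so the promised 95% interval is attainable. Only an adjusted estimate is lacking.
- *It is the least efficient method available.* Against the t-test under normality its efficiency is about 3/π, or 95%. It is less efficient than a baseline-adjusted analysis, and no more than that is claimed.
- *The omission of T1 and mH&Y is peculiar to the rank test.* The article's ANCOVA lists neither. What the rank test loses relative to that ANCOVA is gender, age and disease duration.
- *All clinical outcomes are affected.* TUG, 6-MWT, 10MWT, 5TSTS, gait analysis and TMT are timed, distance or instrumented measures. The article does not classify its instruments, so placing particular symptom totals under the ordinal rule is an inference.

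What remains is that the article names a specific test that cannot use the strata or covariates, although the data needed to adjust are already collected.

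**Conclusion.** The point holds as a matter of precision, not validity. The article commits ordinal-scale secondary outcomes to a test that uses neither the stratification factor nor any covariate, and uses T1 at most by subtraction. Rank ANCOVA on T1 matched or beat both forms of the rank-sum test at every correlation examined. Under the stated assumptions the cost ranges from nothing (changes ranked, r = 0.8, one of the two simulations) to about 38 power points (T2 scores ranked, r = 0.8).

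The direction of the result is secure. Its size depends on the assumed effect, on the assumed correlation, and on which variable is ranked, which the article leaves open. The change should be made, but the trial's validity does not depend on it.

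**What to change.** In the Data analysis section, for secondary outcomes on ordinal scales:

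1. Make the main analysis a rank ANCOVA or proportional-odds model of the T2 score, and likewise of the T3 score, adjusted for the T1 score of the same scale, mH&Y stratum, gender, age and disease duration.
2. Report an adjusted effect estimate with a 95% confidence interval where the model gives one.
3. Keep the rank-sum test, with a Hodges-Lehmann interval, as a sensitivity analysis, and say whether it ranks T2/T3 scores or changes.
4. Name T1 score and mH&Y stratum explicitly. A reference to the existing ANCOVA would not bring them in.
5. List which instruments count as ordinal.

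This needs no new data, since T1 scores and mH&Y stage are already recorded. The cost is a change of wording, slightly more analysis work and, for the proportional-odds model, an assumption to check. It should be settled before any unblinded analysis.

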**Methods:**

A total of 72 participants will be randomly allocated to two different groups, experimental (n = 36) and control group (n = 36). The rehabilitation program will last 6 consecutive weeks and will involve the execution of a total of 30 sessions, one for each day of the week from Monday to Friday. Participants allocated to the control group will carry out a home-based self-treatment program that includes muscle-stretching and active mobilization exercises for 40’/day for 6 consecutive weeks. The primary outcome measure is the effects of both treatments on a new set of molecular biomarkers such as oligomeric alpha-synuclein and neurotrophic factors measured in peripheral neural derived extracellular vesicles (NDEVs). Secondary outcomes will include changes of motor and non-motor symptoms, balance and gait performance and cognitive functioning. This RCT has been registered as “Intensive Multidisciplinary Rehabilitation and Biomarkers in Parkinson’s Disease” on 30 May, 2022 to ClinicalTrials.gov with the Study ID number: NCT05452655.

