A recent phase 2 clinical trial in de novo PD patients compared moderate (60%-65% maximum heart rate), high-intense (80%-85% maximum heart rate) endurance exercise and usual care 4 days per week for 6 months. The clinical outcome was 6-month change in UPDRS Part III. Compared to usual care, high-intensity treadmill exercise resulted in fewer motor changes. Interestingly, the high-intensity group experienced an increase in maximal aerobic power ($\dot{V}o2\max$) compared with baseline [22].

In a recent single-center, double-blind, randomized controlled trial (Park-in-Shape) the authors aimed to evaluate the effectiveness of aerobic exercise delivered at home on relieving motor symptoms in PD subjects with mild disease severity. According to the authors, patients with mild disease severity can reduce off-state motor symptoms by performing aerobic exercise at home [23].

Non-pharmacologic treatment has not only been shown to affect symptomatology, but there is also preliminary evidence in favor of an effect of physical exercise on brain plasticity [24–26]. In particular, the effects of exercise could affect several plasticity-related aspects, among which synaptogenesis, angiogenesis, and neurogenesis [27, 28]. Results on animal models reveal that physical exercise causes changes in neurotrophic factors (NFs) [29–31]. On the same line, there are few studies in the literature linking the benefits of aerobic exercise in PwPD to the involvement of plasticity processes, such as increases in serum brain-derived neurotrophic factor (BDNF) [32] and BDNF-tyrosine receptor kinase B (TrkB) levels [33]. However, the paucity of studies in the literature and their methodological pitfalls do not allow solid conclusions on a potential increase of NFs levels in PD [26].

The absence of methodologically solid studies on the effect of multidisciplinary interventions and their effect on biomarkers points to the need for new standardized controlled randomized clinical trials on this topic.

Moreover, there is still a high level of heterogeneity among studies regarding the detection of α-synuclein as a main biomarker in PD patients [34]. For this reason, in addition to α-synuclein, we have included as a co-primary outcome a set of biological markers closely interconnected with α-synuclein in the PD pathological processes.

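### The 80% power is stated for one biomarker at an unadjusted 0.05, so it is unsupported for the planned FDR analysis of 14 primary biomarkers at two unranked time points

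*Protocol article*

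**What the plan says.** **Sample size.** The plan states "considering 2 degrees of freedom with 80% power; 0,05 alpha and a drop-out percentage of 20" per cent, and concludes "we planned a sample size of N = 72 (N for each group = 36"). The assumptions come from a cross-sectional comparison of people with Parkinson's disease and healthy controls, whose main objective concerned oligomeric alpha-synuclein in neural-derived vesicles. No effect size, standard deviation or test is given, and multiplicity is not mentioned.

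**Primary outcome.** The Outcomes and measurement section gives it as "changes in molecular biomarkers levels (blood biomarkers and serum NDEVs derived biomarkers"). Table 1 then lists the analytes:
- eight in vesicles: alpha-synuclein, STX-1A, VAMP-2, SNAP-25, BDNF, pro-BDNF, GDNF, CDNF;
- six cytokines: IL-1β, TNFα, IFN-γ, IL-6, IL-18, IL-10.

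The abstract names, as examples, "oligomeric alpha-synuclein and neurotrophic factors measured in peripheral neural derived extracellular vesicles (NDEVs"). It mentions no cytokines. The Introduction says "in addition to α-synuclein, we have included as a co-primary outcome a set of biological markers closely interconnected with α-synuclein".

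**Analysis.** An ANCOVA is applied at the end of treatment and again at the end of follow-up, with neither given priority. On multiplicity: "Estimates of primary outcomes will be adjusted using False Discovery Rate correction". Significance is set at p < 0.05.

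**The concern.** The sample-size section and the analysis section describe different tests. One is a single comparison at 0.05. The other is a panel of 14 comparisons, done at two time points, in which each p-value must pass a stricter threshold unless many other markers are also positive. An analysis plan could define the FDR family in detail, but it could not make the published power statement apply to that analysis.

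Two related points blur what counts as success. With no primary time point, a marker that is positive at T2 and not at T3 (or the reverse) has no stated reading. And *co-primary* is commonly understood to mean that every component must succeed, whereas an FDR rule lets any marker succeed by itself. These are different success criteria with very different power.

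**Working it through.** **Inputs from the document.** Alpha 0.05 (two-sided assumed), power 80%, dropout 20%, 36 per arm, 1:1 allocation; 8 + 6 = 14 primary analytes; two time points, so up to 14 × 2 = 28 tests.

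**Reproducing N = 72.** This cannot be done forwards, because there is no effect size or SD. The stated 2 degrees of freedom does not help either, since a two-arm contrast has 1. I therefore solved for the effect that the stated figures imply.

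- Evaluable per arm: 36 × 0.8 = 28.8, about 29.
- d = (z₀.₉₇₅ + z₀.₈₀) × √(2/29) = (1.960 + 0.842) × 0.2626 = 0.74 (0.75 with the t distribution).

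This d is an assumption. It is the value at which the plan's 80% would be true for one unadjusted test.

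**Lone responder.** If only alpha-synuclein responds, its p-value must essentially pass the first Benjamini-Hochberg step, 0.05/m. Normal approximation: power = Φ(2.802 − z₁₋ₐ/₂) with a = 0.05/m.

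- m = 14: a = 0.00357, z = 2.914, Φ(−0.11) = 45.5% (43.2% by noncentral t).
- m = 28: a = 0.00179, z = 3.123, Φ(−0.32) = 37.4% (34.6% by noncentral t).

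**More than one responder.** The Benjamini-Hochberg threshold for the k-th smallest p-value is 0.05k/m, so it relaxes as more markers respond. Simulation used 60,000 runs, the same d for every responding marker, and correlation between markers of 0, 0.3 and 0.6. Ranges run over those correlations and, where lower, include the t-based values.

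| Power for alpha-synuclein, 14 tests | 29 per arm | 36 per arm (no dropout) |
|---|---|---|
| Unadjusted, one test | 80% | 88% |
| It alone responds | 43–46% | 57–59% |
| 7 of 14 respond | 63–67% | 76–79% |
| All 14 respond | 73–77% | 83–87% |

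With one family of 28 tests and 29 per arm, the lone-responder figure falls to about 35–38%. If all 28 effects are real, it is again about 73–77%.

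**At least one true finding (14 tests, 29 per arm).** With 4 true effects this is 93% for independent markers, 85% at correlation 0.3 and 75% at 0.6. With 7 it is 99%, 93% and 83%.

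**Co-primary read as all must succeed.** With all 14 effects real and each test at 80% power, independence gives 0.8¹⁴ = 4.4%. By simulation it is about 21% at correlation 0.3 and 39% at 0.6.

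**The case against.** The strongest reply is that FDR is not Bonferroni. The Introduction describes the markers as closely linked, so a lone responder is the extreme case, and the loss may be small. The Discussion also expects minimal dropout; with 36 per arm and all markers responding, power for alpha-synuclein is above 80%. If the aim is to find some effect in the panel, power can be above 80% with 20% dropout too. All of this stands, and it is why the result must be given as a range. It does not rescue the stated figure, because the Sample size section invokes none of these conditions and itself plans for 20% dropout.

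A reader might go further than the document allows in four ways.

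- *The primary set is defined in three incompatible ways.* The abstract's list is introduced as examples and the Introduction is background; Table 1 is the only full list and is the operative one. What remains is loose wording: vesicle markers only against vesicle markers plus cytokines, and *co-primary* against FDR.
- *The FDR family could be picked after seeing the data.* Whether T2 and T3 form one family or two is ordinary analysis-plan content, and that plan is not shown. The article does describe testing at both times without ranking them.
- *Alpha-synuclein must become the sole primary test.* The Introduction gives a reason for the panel: inconsistent detection of alpha-synuclein across studies. A single primary is a legitimate option, not a required correction.
- *Saying that estimates are adjusted shows a faulty method.* It is a wording slip; FDR procedures act on p-values.

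**Conclusion.** The point holds as a mismatch between sizing and analysis: the 80% is unsupported for the analysis that is planned. At 29 evaluable per arm, every scenario examined put alpha-synuclein below 80%, from a loss of 3–7 percentage points if all 14 markers respond to about 34–37 points if it alone does (14 tests).

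A reader might infer that the true power is 43%, or that 80% has been shown to be false. Neither follows. The document gives no effect size, so even the unadjusted 80% cannot be checked, and 43% belongs to a single scenario.

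The figures rest on a back-solved d of about 0.75, two-sided testing, a two-sample comparison without any precision gain from ANCOVA covariates, equal effects in all responding markers, and equal correlation between markers. That alpha-synuclein was the marker used for sizing is inferred from the main objective of the source study.

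**What to change.** 1. In Data analysis, name T2 as the primary time point and T3 as secondary.
2. State that the 14 analytes of Table 1 at T2 form the one primary FDR family, controlled at 5% by Benjamini-Hochberg, and that p-values, not estimates, are adjusted.
3. In Sample size, replace the unqualified 80% with the power range under FDR, giving the assumed effect, the number of responding markers and the dropout. On the assumptions above, for alpha-synuclein at 29 per arm: about 43–46% (alone), 63–67% (seven respond), 73–77% (all 14).
4. In the Introduction, replace *co-primary* with wording that fits the FDR rule, and align the abstract's description with Table 1.

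The investigators may instead choose alpha-synuclein at T2 as the single primary test. That would keep the sizing at 0.05 coherent, but 13 markers would lose primary status, against the Introduction's reason for including them.

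The cost is wording in the protocol and a matching registry update, made before group results are seen. No extra participants are needed. The downside is that the stated power becomes less favourable and T3 results carry secondary weight.
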